## Abstract

**Background:**

Surfactant is a well-established therapy for preterm neonates affected by respiratory distress syndrome (RDS). The goals of different methods of surfactant administration are to reduce the duration of mechanical ventilation and the severity of bronchopulmonary dysplasia (BPD); however, the optimal administration method remains unknown. This study compares the effectiveness of the INtubate-RECruit-SURfactant-Extubate (IN-REC-SUR-E) technique with the less-invasive surfactant administration (LISA) technique, in increasing BPD-free survival of preterm infants. This is an international unblinded multicenter randomized controlled study in which preterm infants will be randomized into two groups to receive IN-REC-SUR-E or LISA surfactant administration.

**Methods:**

In this study, 382 infants born at 24^+0^–27^+6^ weeks’ gestation, not intubated in the delivery room and failing nasal continuous positive airway pressure (nCPAP) or nasal intermittent positive pressure ventilation (NIPPV) during the first 24 h of life, will be randomized 1:1 to receive IN-REC-SUR-E or LISA surfactant administration. The primary outcome is a composite outcome of death or BPD at 36 weeks’ postmenstrual age. The secondary outcomes are BPD at 36 weeks’ postmenstrual age; death; pulse oximetry/fraction of inspired oxygen; severe intraventricular hemorrhage; pneumothorax; duration of respiratory support and oxygen therapy; pulmonary hemorrhage; patent ductus arteriosus undergoing treatment; percentage of infants receiving more doses of surfactant; periventricular leukomalacia, severe retinopathy of prematurity, necrotizing enterocolitis, sepsis; total in-hospital stay; systemic postnatal steroids; neurodevelopmental outcomes; and respiratory function testing at 24 months of age. Randomization will be centrally provided using both stratification and permuted blocks with random block sizes and block order. Stratification factors will include center and gestational age (24^+0^ to 25^+6^ weeks or 26^+0^ to 27^+6^ weeks).

Analyses will be conducted in both intention-to-treat and per-protocol populations, utilizing a log-binomial regression model that corrects for stratification factors to estimate the adjusted relative risk (RR).

**Discussion:**

This trial is designed to provide robust data on the best method of surfactant administration in spontaneously breathing preterm infants born at 24^+0^–27^+6^ weeks’ gestation affected by RDS and failing nCPAP or NIPPV during the first 24 h of life, comparing IN-REC-SUR-E to LISA technique, in increasing BPD-free survival at 36 weeks’ postmenstrual age of life.

**Trial registration:**

ClinicalTrials.gov NCT05711966. Registered on February 3, 2023.

**Supplementary Information:**

The online version contains supplementary material available at 10.1186/s13063-024-08240-4.

## Administrative information

Note: The numbers in curly brackets in this protocol refer to the SPIRIT checklist item numbers. The order of the items has been modified to group similar items (see http://www.equator-network.org/reporting-guidelines/spirit-2013-statement-defining-standard-protocol-items-for-clinical-trials/).

**Table Taba:** 

Title {1}	Comparison of “IN-REC-SUR-E” and LISA in preterm neonates with respiratory distress syndrome: a randomized controlled trial (IN-REC-LISA trial)
Trial registration {2a and 2b}	ClinicalTrials.gov Identifier: NCT05711966. Status: recruiting. First Posted: 3/02/2023; Last update posted: 17/02/2023
Protocol version {3}	Version 3, 25 October 2022
Funding {4}	The study has received economic contributions by way of partial coverage of the expenses relating to its implementation

## Introduction

### Background and rationale {6a}

Respiratory distress syndrome (RDS) represents the main cause of respiratory insufficiency in preterm infants and is one of the major causes of perinatal morbidity and mortality. Surfactant is a well-established therapy in neonatology. However, the optimal surfactant administration method remains unresolved, especially with the recent clinical focus on avoiding mechanical ventilation in preterm infants born before 28 weeks’ gestational age (i.e., extremely preterm infants). Duration of mechanical ventilation is a key determinant of the severity of bronchopulmonary dysplasia (BPD) [1]. Although attractive and beneficial in clinical practice, the INtubate, SURfactant, Extubate (IN-SUR-E) method cannot be universally applied to all preterm neonates due to non-homogeneous surfactant distribution and lung derecruitment during intubation, resulting in failure of IN-SUR-E in the event of severe RDS. IN-SUR-E also has a failure rate in preterm infants ranging from 19 to 69% [2, 3]. Risk factors for failure of IN-SUR-E are low birth weight, low gestational age, the severity of initial respiratory disease, and a low hemoglobin concentration prior to surfactant administration [2, 4, 5]. A recent randomized clinical trial showed that the application of a recruitment maneuver just before surfactant administration, followed by rapid extubation (INtubate-RECruit-SURfactant-Extubate [IN-REC-SUR-E]), decreased the need for mechanical ventilation during the first 72 h of life compared with IN-SUR-E technique in extremely preterm neonates, without increasing the risk of adverse neonatal outcomes [6]. Recently, a less-invasive surfactant administration (LISA) method was developed with surfactant introduced into the trachea of infants breathing spontaneously using a small catheter instead of an endotracheal tube [7]. The popularity of the LISA technique has increased because it potentially combines the benefits of early surfactant treatment with continuous positive airway pressure (CPAP) and consequent avoidance of mechanical ventilation. The last network meta-analyses on the comparative efficacy of methods for surfactant administration found that among preterm infants, the LISA technique was associated with a lower likelihood of mortality, need for mechanical ventilation, and BPD compared with IN-SUR-E, but these findings did not include a comparison to the IN-REC-SUR-E method [8]. More importantly, data for neonates < 28 weeks’ gestation are not as robust as for the higher gestational age groups due to a smaller number of neonates [9]. Therefore, the safety and efficacy of LISA in this population remain to be confirmed, also considering that extreme prematurity is an independent risk factor for LISA failure [10]. The same authors of meta-analysis agree that data for neonates < 28 weeks are not as robust as for higher gestation age group and that lung recruitment before surfactant administration (IN-REC-SUR-E) represents a promising novel alternative; hence, future randomized evidence directly comparing it to LISA is warranted to draw conclusions concerning the optimal method of surfactant treatment, especially among extremely low gestational age newborns [11]. We therefore designed this study to compare the IN-REC-SUR-E technique with LISA, as recently suggested [11, 12], for evaluating the comparative effectiveness of these techniques in increasing the survival without BPD of extremely preterm infants.

### Objectives {7}

The primary hypothesis of this study is that IN-REC-SUR-E via a high-frequency oscillatory ventilation recruitment maneuver increases survival without BPD at 36 weeks’ postmenstrual age in spontaneously breathing infants born at 24^+0^–27^+6^ weeks’ gestation and failing nasal CPAP or nasal intermittent positive pressure ventilation (NIPPV) during the first 24 h of life compared to LISA treatment.

To confirm this hypothesis, we planned an international multicenter randomized controlled study in which preterm infants will be randomized into two groups: one will receive surfactant with IN-REC-SUR-E modality, and the other one will receive surfactant with LISA treatment.

The study flow chart is detailed in Fig. 1.

**Fig. 1 Fig1:**
[figure not shown]
Study flow chart

### Trial design {8}

The study is an unblinded multicenter randomized superiority trial of the IN-REC-SUR-E vs. LISA technique in infants born at 24^+0^–27^+6^ weeks’ gestation.

The methods of this study are reported according to SPIRIT 2013 Explanation and Elaboration: Guidance for protocols of clinical trials [13].


### Eligibility criteria {10}

#### Inclusion criteria

Infants satisfying the following inclusion criteria will be eligible to participate:Born at 24^+0^–27^+6^ in a tertiary neonatal intensive care unit participating in the trialBreathing independently and sufficiently with only nasal CPAP or NIPPV for respiratory supportWritten parental consent has been obtainedFailing nasal CPAP or NIPPV during the first 24 h of life

#### Exclusion criteria

The following are the exclusion criteria:Severe birth asphyxia or a 5-min Apgar score of less than 3Prior endotracheal intubation for resuscitation or insufficient respiratory driveProlonged (> 21 days) premature rupture of membranesPresence of major congenital abnormalities with possible effects on cardiorespiratory functionHydrops fetalisInherited disorders of metabolism

### Who will take informed consent? {26a}

The fully trained specific researchers who are on-site will obtain informed prospective consent from participants. Written and oral information will, whenever possible, be offered to parents prior to birth if the mother is at risk for preterm delivery and the infant is likely to be eligible. Informed written consent will be signed by both parents, and sufficient time will be provided for consent. If parents do not speak the local language, consent will only be obtained if an independent interpreter is available. The informed consent will be obtained by the principal investigator of each participating center and their collaborators in charge. A senior investigator will be always available to discuss concerns raised by parents or clinicians during the course of the trial.

### Additional consent provisions for collection and use of participant data and biological specimens {26b}

No additional consents are required. This trial does not involve collecting biological specimens for storage.

### Interventions

#### Explanation for the choice of comparators {6b}

Infants will be allocated to one of the two treatment groups (1:1) according to a restricted randomization procedure [14]. A study investigator (TP) will generate the allocation sequences using both stratification and permuted blocks with random block sizes and block order. The assignment to intervention will be unmasked to all trial participants: parents, research staff, and medical team will be only aware of the study group assignment after randomization procedures.

#### Intervention description {11a}

##### Management in the delivery room

Neonates will be stabilized after birth with positive pressure using a neonatal mask and a T-piece system (for example, Neopuff Infant Resuscitator ®, Fisher and Paykel, Auckland, New Zealand). All neonates will be started on nasal CPAP of at least 6 cmH_2_O via mask or nasal prongs [15]. Newborns who do not breathe or who are persistently bradycardic (heart rate less than 100/min) within the first 60 s after birth will receive positive-pressure ventilation at a rate of 40 to 60 inhalations/min [15] with initial FiO_2_ of 0.30. Infants that will be transitioned successfully to spontaneous breathing will be transferred to the neonatal intensive care unit on nasal CPAP (6–7 cm H_2_O) or NIPPV (PEEP 6–7 cmH_2_O, PIP 12–15 cmH_2_O, respiratory rate 30–40 breaths/min). The decision to intubate and start invasive mechanical ventilation in the delivery room will be in accordance with the American Heart Association Guidelines [16].

The method and timing of umbilical cord clamping will be as per standard practice at each site.

##### CPAP or NIPPV failure criteria

Nasal CPAP or NIPPV will be administered in the neonatal intensive care unit via nasal prongs or nasal mask using the standard method of each participating center, with a pressure of 7–8 cmH_2_O or with a setting of peak inspiratory pressure of 12–15 cmH_2_O, positive end-expiratory pressure of 7–8 cmH_2_O, and rate of 30–40 breaths/min. Infants will receive surfactant with IN-REC-SUR-E or LISA if they need a FiO_2_ of 0.30 or greater to maintain a SpO_2_ between 90 and 94% for at least 30 min, regardless of the non-invasive respiratory support used (CPAP or NIPPV). Infants will also be given surfactant if their clinical status deteriorates rapidly characterized by a rapid increase in oxygen requirements or if they will develop respiratory acidosis defined as a pCO_2_ more than 65 mmHg (8.5 kPa) and a pH less than 7.20, or with lung ultrasound scoring > 8.

A loading dose of intravenous caffeine citrate (20 mg/kg) will be given in the delivery room or immediately after admission to the neonatal intensive care unit (within 2 h of life) and always prior to surfactant administration, followed by a morning intravenous/oral dose of 5–10 mg/kg/day as required.

If a patient, before non-invasive ventilation failure criteria and randomization, will develop severe apnea (more than four episodes of apnea per hour or more than two episodes of apnea per hour requiring ventilation with bag and mask), despite optimal nasal CPAP, nasal intermittent positive pressure ventilation, or bilevel positive airway pressure, the baby will no longer be eligible for the study.

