##### LISA group

By contrast, infants allocated to the LISA group will receive 200 mg/kg of poractant alfa (Chiesi Farmaceutici S.p.A., Parma, Italy) according to the following protocol: during nasal CPAP with a pressure of 7–8 cm H_2_O, surfactant will be administered over 0.5–3 min using the SurfCath™ tracheal instillation catheter (VYGON S.A. – Ecouen, France), or a 4–6-F end-hole catheter, according to local protocols. After pre-procedural medications, the catheters will be positioned during laryngoscopy with or without Magill forceps. The catheter will be connected to a syringe pre-filled with the surfactant, and the surfactant is instilled slowly. The infant’s mouth will be closed. In cases of apnea or bradycardia, positive pressure ventilation will be performed until recovery by nasal prongs or mask or by endotracheal tube if necessary. After surfactant administration, CPAP (7–9 cm H_2_O) [19] or NIPPV will be provided unless failure criteria are met (see below).

Transcutaneous PaCO_2_ will be recorded during surfactant administration in both procedures (IN-REC-SUR-E and LISA), if available. Changes in respiratory support settings are permitted to maintain transcutaneous CO_2_ values in each site’s accepted range.

In both groups, maintaining a FiO_2_ < 0.30 to obtain SpO_2_ values in the desired range (90–94%) will drive weaning of the level of CPAP or in the rate of NIPPV in the following days. In the babies managed with CPAP, the decision as to whether to begin bilevel-positive airway pressure or NIPPV to prevent the need for re-intubation in infants of both groups will be up to the neonatologist on duty and will be considered in the final analysis.

Infants in both groups who meet the CPAP/NIPPV failure criteria again during the following 24 h will receive a second dose of surfactant (100 mg/kg of poractant alfa) according to the randomized group (IN-REC-SUR-E or LISA). The minimum time interval between the first and second doses of surfactant is 6 h. In case of respiratory deterioration requiring endotracheal intubation immediately after the first surfactant administration, this will be interpreted as extubation failure in the INRECSURE group or as severe respiratory failure requiring intubation in the LISA group.

The indications for invasive mechanical ventilation via endotracheal tube after IN-REC-SUR-E or LISA will be as follows:

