Poor oxygenation with FiO_2_ above 0.40 for more than 6 h to maintain a SpO_2_ between 90 and 94% despite CPAP (7–9 cm H_2_O) or NIPPV (with peak inspiratory pressure of 15–20 cmH_2_O, positive end-expiratory pressure of 6–8 cmH_2_O, and rate of 40–60 breaths/min)Respiratory acidosis (either capillary pCO_2_ or PaCO_2_ > 65 mm Hg [8.5 kPa] and pH < 7.20)Apnea (more than four episodes of apnea per hour or more than two episodes of apnea per hour requiring ventilation with bag and mask), despite optimal nasal CPAP, nasal intermittent positive pressure ventilation, or bilevel positive airway pressure

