### Participant timeline {13}

All participants will complete the same outcome assessments as presented in Fig. 1 and Table 1.

**Table 1 Tab1:** Overview of enrolment, interventions, and assessments

	Study period					
	Enrollment	Allocation	Post-allocation			Close-out
Time point	* − t*_*1*_	0	*t*_*1*_	*t*_*2*_***	*t*_*3*_	*t*_*4*_
Enrollment						
Eligibility screen	X					
Informed consent	X					
Allocation		X				
Interventions						
*INRECSURE group*			X	X	X	X
*LISA group*			X	X	X	X
Assessments						
*Information on background and randomization*	X					
*Primary outcome*					X	
*Secondary outcomes*			X	X	X	X
*Other collected data*	X					

− *t*_*1*_ before or after birth, *0* at the time of allocation, *t*_*1*_ first surfactant administration within 2 h of life, *t*_*2*_*** possible second dose of surfactant during the following 24 h after the first dose, *t*_*3*_ at discharge or death, *t*_*4*_ follow up at 24 months of age

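### The kPa value printed for the acidosis limit does not equal 65 mmHg, and Table 1 times first surfactant within 2 h of life although eligibility runs to 24 h

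*Protocol article*

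**What the plan says.** **Acidosis limit.** In the section on CPAP or NIPPV failure criteria, one of the routes to surfactant is respiratory acidosis, defined as pCO2 "more than 65 mmHg (8.5 kPa) and a pH less than 7.20". The list of indications for invasive mechanical ventilation, at the end of the LISA group section, uses the same limit: capillary or arterial pCO2 "> 65 mm Hg [8.5 kPa] and pH < 7.20".

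**Timing of first surfactant.** The footnote to Table 1 (Participant timeline {13}) defines t1 as "first surfactant administration within 2 h of life". The eligibility text sets a different window. The abstract's Methods paragraph describes infants "failing nasal continuous positive airway pressure (nCPAP) or nasal intermittent positive pressure ventilation (NIPPV) during the first 24 h of life", its Discussion paragraph says "failing nCPAP or NIPPV during the first 24 h of life", and Objectives {7} says "failing nasal CPAP or nasal intermittent positive pressure ventilation (NIPPV) during the first 24 h of life". The inclusion criteria give the same 24 h. The only other 2 h limit is the one for the caffeine loading dose, to be given in the delivery room or "immediately after admission to the neonatal intensive care unit (within 2 h of life").

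**Second dose (for the side note).** The LISA group section states: "Infants in both groups who meet the CPAP/NIPPV failure criteria again during the following 24 h will receive a second dose of surfactant". The dose follows the allocated technique and comes at least 6 h after the first.

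**The concern.** The acidosis limit decides treatment twice, once for giving surfactant and once for intubating. Two printed values that are not equivalent give an international trial two limits, depending on the unit in which a center reports blood gases.

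The Table 1 footnote is the schedule that sites and data managers work from. An infant who first fails CPAP at, say, hour 10 is eligible under the inclusion criteria, yet any dose given then falls outside the only time label for first surfactant. Left alone, this invites needless queries in the eCRF or an unintended belief that late failures should not be enrolled.

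**Working it through.** **1. Unit conversion**

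Inputs: 65 mmHg and 8.5 kPa (failure criteria and ventilation indications); 1 mmHg = 0.133322 kPa (a unit definition, not taken from the documents).

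- Attempt to reproduce the printed value: 65 × 0.133322 = 8.666 kPa, or 8.7 to one decimal. The printed 8.5 is not reproduced.
- Reverse: 8.5 / 0.133322 = 63.76 mmHg.
- Size of the gap: 65 − 63.76 = 1.24 mmHg; 8.666 − 8.5 = 0.166 kPa; 0.166 / 8.666 = 1.9%.
- Rounding as an explanation: values that round to 8.5 kPa lie between 8.45 / 0.133322 = 63.4 mmHg and 8.55 / 0.133322 = 64.1 mmHg. 65 mmHg is outside that range.
- Check of the correction: 8.7 / 0.133322 = 65.26 mmHg, so 0.26 mmHg of ordinary rounding remains.

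The infants affected are those with pCO2 between 63.8 and 65 mmHg who also have pH below 7.20, at sites that read kPa.

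**2. Timing of first surfactant**

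| Place | Limit | Applies to |
|---|---|---|
| Abstract (Methods, Discussion), Objectives {7}, Inclusion criteria | first 24 h of life | CPAP/NIPPV failure |
| CPAP or NIPPV failure criteria | within 2 h of life | caffeine loading dose |
| Table 1 footnote, t1 | within 2 h of life | first surfactant |

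Surfactant is given when the failure criteria are met, so first dosing can fall anywhere in the 24 h window. Hours of that window outside the label: 24 − 2 = 22. This is a share of time, not of infants; the documents give no distribution of failure times. Four statements agree on 24 h, so the footnote is the outlier.

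**3. Side note: re-dosing and ventilation**

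The second-dose rule can operate from 6 h (minimum interval) to 24 h after the first dose, a span of 24 − 6 = 18 h. In that span an infant with pCO2 above 65 mmHg and pH below 7.20 meets both the repeat-failure rule and a ventilation indication. The same can happen through oxygen: an infant above FiO2 0.40 for more than 6 h has also needed at least 0.30 for 30 min. How many infants this concerns cannot be derived from the document.

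**The case against.** The best defence is that neither error does much. The kPa figure stands in parentheses behind a clear mmHg value, differs by 1.2 mmHg, and matters only when pH is also below 7.20. Acidosis is one of several routes to surfactant. A center presumably uses one unit for all its infants, and randomization is stratified by center, so the shift falls on both arms alike. The Table 1 label is a schedule entry and does not set eligibility. All of this stands, and it limits the size of the point. It does not make either statement correct.

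Two stronger readings are tempting, and the document supports neither.

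- *A reader might infer that a dose after 2 h would be a protocol deviation and remove infants from the per-protocol population.* Nothing in the article defines a deviation by dose time, and the eligibility criteria use 24 h.
- *A reader might infer that re-dosing and intubation contradict each other in both arms, and only for acidosis.* In the IN-REC-SUR-E arm a second dose by the allocated technique itself involves intubation, and that section reserves extubation for infants who are breathing adequately and are stable. In the LISA arm, the statement that non-invasive support continues until failure criteria are met refers the reader to a later place, most naturally the list of ventilation indications. Acidosis is not special either, as the oxygen example shows. The preparatory meetings and the check that procedures are followed similarly across centers further limit drift. What remains is that the LISA text does not say outright whether such an infant is re-dosed, intubated or both.

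**Conclusion.** Both statements are wrong as written and should be corrected; the consequence is small. The printed kPa value is 0.17 kPa (1.9%) too low, equivalent to acting about 1.2 mmHg earlier at a site that reads kPa. The t1 label covers 2 of the 24 hours in which first surfactant can be indicated. The sample size, the primary outcome definition and the primary analysis are unaffected, and no effect on the analysis populations is claimed.

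The first conclusion rests only on the unit conversion. The second rests on reading the repeated 24 h window as the intended one. The open order of re-dosing and intubation in the LISA arm is a request for clarification. It could touch only two secondary outcomes, need for invasive support and receipt of two or more surfactant doses, to an extent that cannot be quantified here.

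**What to change.** 1. Print 65 mmHg (8.7 kPa) in the CPAP or NIPPV failure criteria and in the indications for invasive ventilation.
2. Relabel t1 in the Table 1 footnote as first surfactant at CPAP/NIPPV failure within the first 24 h of life.
3. As a side note, have the sponsor state what it intends for a LISA infant who meets a ventilation limit 6 to 24 h after the first dose: re-dose, intubate, or both, and in what order. No rule that withholds the second dose is proposed. The protocol says infants who fail again receive it, and removing it would change treatment, which goes beyond clarification.

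Items 1 and 2 cost one clarification letter and a matching eCRF check, with no added patients or time. Item 3 can go in the same letter if it only records existing intent. If the sponsor's answer changes treatment, it would need ethics committee approval under the article's section on communicating important amendments {25}.
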